## Methods

### Study design

This is a multicenter controlled randomized clinical trial in four parallel groups: a) healthy lifestyle psychoeducational program, b) focused program on positive affect promotion, c) brief intervention based on mindfulness and d) improved treatment as usual (ITAU) group in primary care.

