### Interventions

All interventions (except ITAU) are composed of one face-to-face group session and 4 online, individual and interactive therapeutic modules.

Face-to-face session will involve 3-5 patients and will be 90 minutes in length. The aim of this session will be to explain the program structure and main components of treatment, and to motivate participants for change.

The online therapeutic modules are oriented to work on different psychological techniques and the duration of each module will be approximately 60 minutes. All modules include an explanation of the module contents, check questions to test if they understand the contents and exercises to practice such techniques. These modules are sequential, in order to move step by step, all along the program. However, user can review the module contents once they are finished. Duration of the program can vary among users, it is estimated the duration for most people will be 4-8 weeks. The participants will receive two weekly-automated mobile phone messages, encouraging them to proceed with the program and reminding them of the importance of doing the tasks in each module. Furthermore, the participants will receive an automated e-mail encouraging them to continue with the modules if they have not accessed the program for a week. The program also offers continued feedback to users through the assessment tools showing them their progress throughout the entire treatment process.

All groups of patients will receive treatment as usual improved by their GPs, as described below in this section. All groups of patients will also receive a participant manual with information about technical aspects of the online program.

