#### Descriptions of costing procedure

Data collection on the use and utilization of health and social services will be collected through the questionnaire Client Service Receipt Inventory (CSRI) Spanish version [40]. The variant to be used in this study was designed to retrospectively collect data on service use during the previous 6 months.

Costs were estimated from the healthcare and societal perspectives during the six months of follow-up. Direct health care costs were calculated by adding the costs derived from medication consumption, medical tests, use of health-related services, and cost of the staff running the CBT intervention.

The cost of medication will be calculated by determining the price per milligram according to the Databases of the drug from the Ministry of Health and Consumer and included the value-added tax. The total costs of medications were calculated by multiplying the price per milligram by the daily dosage used (in milligrams) and the number of days that the treatment was received. The main source of the unit cost data for medical tests and health services will be use the OBLIKUE database of health care costs. The OBLIKUE database contains information about Spanish healthcare service costs and was derived by systematic reviews of the literature; it consists of approximately 18,000 entries.

Indirect costs (lost productivity): Lost productivity will be calculated using the human capital approach, which involves multiplying the minimum daily wage in Spain for 2014 by the number of days of sick leave, as reported by each patient. Finally, total costs were calculated by adding the direct and indirect costs. Unit costs are expressed in Euros (€) based on 2014 prices.

In our study the general guidelines for conducting pharmacoeconomic analyzes in Spain and the International Society for Pharmacoeconomics and Outcomes Research (ISPOR) [47,48] will be followed.

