##### Analysis perspective and time horizon

The perspective used in our analysis will be twofold: on one hand the social perspective, to include all costs and quality of life and moreover the perspective of the national health system.

The time horizon of the study is 12 months, so there will have to use any kind of discount or costs or profits.

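### The only programme line in the cost sum names a CBT intervention that no arm delivers and covers staff only, so online delivery is unpriced and incremental cost against ITAU is understated

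*Protocol article*

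**What the plan says.** All references are to the protocol article.

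- **Descriptions of costing procedure.** Direct health care cost is the sum of medication, medical tests, "use of health-related services, and cost of the staff running the CBT intervention". Total cost is then direct plus indirect cost, and lost productivity is the only indirect item described.
- **Study design.** The four arms are "a) healthy lifestyle psychoeducational program, b) focused program on positive affect promotion, c) brief intervention based on mindfulness and d) improved treatment as usual (ITAU)".
- **Interventions.** "All interventions (except ITAU) are composed of one face-to-face group session and 4 online, individual and interactive therapeutic modules". On the staffed part: "Face-to-face session will involve 3-5 patients and will be 90 minutes in length". On the online part: "the duration of each module will be approximately 60 minutes". On contact during the programme: "The participants will receive two weekly-automated mobile phone messages", with an automated e-mail after a week without access. On length: "it is estimated the duration for most people will be 4-8 weeks".
- **Analysis perspective and time horizon.** Two perspectives are used, that of the national health system and "on one hand the social perspective, to include all costs and quality of life".
- **Cost-utility analysis.** The ICER is the cost difference between two strategies divided by their difference in effect. Acceptability curves are built from the same increments.

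**The concern.** The cost sum has a single line for the programmes themselves, and that line fails in two ways. It names an intervention that is not in the trial. It also covers people only, whereas these are self-guided programmes whose main vehicle is an online platform.

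The unpriced items are not spread evenly over the arms. Modules, reminder messages and reminder e-mails go with the programmes, and ITAU is expressly excepted from the module format. An omission of this kind does not cancel in a comparison with ITAU; it lowers cost on one side. The cost difference is the numerator of the ICER, so the error carries straight into the cost-utility result. The Abstract and Background give possible cost-effectiveness of ICT delivery as part of the reason for the trial, and ICT delivery is the part left without a price.

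**Working it through.** The article states no unit cost, programme cost or ICER, so there is no figure of its own to reproduce. The check compares the cost sum with the programme components and then works out the direction of the error.

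**Step 1. Is any arm CBT?** The arms are healthy lifestyle, positive affect, mindfulness and ITAU. Some modules use behavioural techniques, but none of the programmes is called CBT. The Background mentions a computerised CBT programme studied by the same group, as a separate study. The phrase was probably carried over from there.

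**Step 2. What does the line cover if it means the three programmes?** It covers staff. The one staff-run element described is the group session:
- staff minutes per patient = session length / group size
- 90 / 5 = 18 and 90 / 3 = 30, so 18 to 30 minutes per patient, assuming one staff member per session (the article does not give the number).

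**Step 3. What has no line?**

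| Component | Quantity per programme patient | Line in the cost sum |
|---|---|---|
| Group session, staff | 18-30 min (one staff member assumed) | Yes, if the phrase is read generously |
| Online modules (hosting, maintenance) | 4 × 60 = about 240 min of patient use | None |
| Automated phone messages | 2 × 4 = 8 to 2 × 8 = 16 | None |
| Automated e-mails | depends on gaps in access | None |
| Participant manual | given to all groups | None, but common to all arms |

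The message count reads the text as two messages a week over 4 to 8 weeks. By scheduled patient time, 240 / (240 + 90) = 73% of a programme is online. That is a share of minutes and says nothing about the share of cost.

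The other lines do not pick these items up. The Client Service Receipt Inventory is described as recording use of health and social care services and time off work. It is not described as recording hosting or messaging.

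**Step 4. Direction.** Let ΔC be the incremental cost computed under the stated sum, *c* the omitted delivery cost per programme patient, and *q* the QALY gain over ITAU.
- ICER as computed = ΔC / *q*
- ICER with delivery priced = (ΔC + *c*) / *q*
- understatement = *c* / *q*, for *q* > 0

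If a fraction *u* of ITAU patients takes up the programme within follow-up at the same cost per user, and every programme-arm patient uses it, the understatement becomes *c*(1 − *u*) / *q*. It shrinks and does not change sign while *u* < 1.

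**Step 5. Illustration only.** Neither *c* nor *q* is in the article; both are assumed here.

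| Assumed *c* (EUR) | *q* = 0.01 | *q* = 0.02 | *q* = 0.05 |
|---|---|---|---|
| 5 | 500 | 250 | 100 |
| 50 | 5,000 | 2,500 | 1,000 |
| 200 | 20,000 | 10,000 | 4,000 |

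Entries are EUR per QALY. The spread from 100 to 20,000 shows that the size is unknown; no cell is an estimate.

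**The case against.** The best reply is that this is a wording slip in a condensed article. An analyst facing three programmes would read the phrase as meaning them. The article also commits to all costs under the social perspective and to Spanish and ISPOR guidelines, and an itemised intervention costing could sit in a fuller document. Much of this is fair, and it lowers the likelihood that the final analysis would really leave these costs out. It does not remove the point. The article does not defer the item elsewhere. It states a sum and builds total cost on it, and that sum does not meet its own commitment to all costs.

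A reader might infer more than the document supports:

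- *That programme cost is zero in every arm.* This follows only from a strictly literal reading that an analyst is unlikely to adopt. The point stands without it.
- *That everything left out falls on the programme arms.* The participant manual goes to all groups and roughly cancels; so does GP training, since all patients are treated by their GPs under ITAU.
- *That ITAU should carry a flat programme cost of zero.* Under Ethical aspects, ITAU patients are to be offered the programme, with no timing given. Any who use it within follow-up incur its cost.
- *That the four hours of modules measure the missing cost.* They are patient time on a self-guided programme, not provider resource use.
- *That a stated result is wrong.* The article reports no ICER and says only that the interventions could be cost-effective.

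The reach is also limited. The primary outcome, PHQ-9, is untouched, and comparisons among the three programmes change little because they share one format.

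**Conclusion.** The costing rule is wrong as written. Its only programme line is mislabelled and, on the most favourable reading, leaves the online delivery under evaluation unpriced. Followed as stated, it understates incremental cost against ITAU in all three comparisons by the delivery cost per patient, less whatever ITAU patients incur by taking up the programme. For a positive QALY gain, ICERs and acceptability curves then lean towards the programmes.

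The direction rests on two conditions: the online items have some positive cost, and uptake in the programme arms exceeds uptake in ITAU. The size cannot be derived from the document. It may be small if only hosting and messaging count, and larger if development cost is spread over few users. This should be corrected before the economic analysis, but it concerns a secondary analysis.

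**What to change.** In Descriptions of costing procedure, replace the CBT phrase with *cost of delivering the programme received*, and list what it covers:

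1. staff time of the group session, divided by the number who actually attended;
2. platform hosting and maintenance, per user;
3. automated phone messages and e-mails.

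Charge these by programme actually received, so that an ITAU patient who takes up the programme within follow-up is costed too. Treat the participant manual as common to all arms. State whether one-off development cost is included.

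The change costs a wording edit and a short costing from project accounts; no further outcome data are needed from patients. The price is somewhat less favourable ICERs than the present sum would give.

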#### Utility scores

Utility scores will be obtained from the questionnaires quality of life related to health EuroQol 5D and SF-12. The EQ-5D is used to rate patients’ quality of life on a scale from 0 (as bad as death) to 1 (perfect health). Negative values are possible and indicate a health state that is “worse than death.” QALYs were calculated on the basis of these scores using the Spanish tariffs of EQ-5D [49]. Along with EQ-5D utility scores, scores recorded on the EQ VAS were also used as an outcome for the analysis.

##### Analysis perspective and time horizon

The perspective used in our analysis will be twofold: on one hand the social perspective, to include all costs and quality of life and moreover the perspective of the national health system.

The time horizon of the study is 12 months, so there will have to use any kind of discount or costs or profits.

#### Cost-utility analysis

Cost-utility will be explored through the calculation of incremental cost-effectiveness ratios (ICER), defined as the ratio between incremental costs and incremental effects measured on QALYs or EQ VAS [50]. QALYs were approximated by using the area under-the-curve technique.

To estimate the incremental cost effectiveness ratio - ICER (marginal incremental cost and incremental effects) the following equation is used:$$ ICER=\frac{Cost\  strategy\ 1- Cost\  strategy\ 2}{effectiveness\  strategy\ 1- effectiveness\  strategy\ 2} $$

Cost-effectiveness acceptability curves (CEACs) will also be plotted when necessary [50]. CEACs display the probability that the intervention is cost-effective, given a varying threshold for the willingness to pay for each QALY gained. The curves obtained incorporate the uncertainty that exists around the estimates of incremental costs and incremental effects associated with the intervention [51].

Data collection will be performed using EXCEL software and then for statistical analysis we used the SPSS (SPSS Inc., Chicago, IL, USA) software version 20, licensed for University of Malaga.

Frequency and proportions used for descriptive statistics of categorical or qualitative variables. For quantitative variables the mean and standard deviation were obtained.

For inferential statistical test Chi-square test for qualitative variables for qualitative and quantitative variables was used test one-way ANOVA, and for the test of the T-Student quantitative variables. In all cases statistical significance corresponded to a value of p <0.05.

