### Recruitment

The recruitment strategy will be performed in primary care settings by participating GPs among patients fulfilling study criteria. When the GP identifies a potential participant, he/she will explain the patient the characteristics of the study. Whether the patient is interested in participating he/she will sign an informed consent and the GP will fill a referral form describing the sociodemographic characteristics of the patient and a checklist for inclusion/exclusion criteria, and will give him/her the patient’s information sheet and a handout describing the study. If the patient does not want to participate or does not meet inclusion criteria, the GP will fill the referral form describing the reason for not including him/her. The GP will send these documents by fax to the local researcher. Subjects will be interviewed in the next 3 days by the researcher. After confirming that they have signed the informed consent and have understood the study and the treatment options, the researcher will administer the psychological assessment instruments related with inclusion criteria: MINI International Neuropsychiatric Interview [33], PHQ-9 [29] and sociodemographic variables. The researcher will collect baseline data and will contact an independent researcher to implement the randomization.

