**Table 1 Tab1:** **Study variables**

**Instrument**	**Assessment area**	**Time of assessment**	**Applied by**
MINI Neuropsychiatric interview	Psychiatric diagnosis	Baseline	Researcher A
PHQ-9	Severity of depression	Baseline and follow-up sessions*	Researcher A (baseline) Online (follow-up sessions)
Sociodemographic data	Gender, age, marital status, education, occupation, economical level	Baseline	Researcher A
SF-12 Health Survey	Health-related quality of life	Baseline and follow-up sessions*	Online
CRSI	Health and social services use	Baseline and 6 and 12 post-treatment months	Researcher A (baseline) Researcher B (6 and 12 post-treatment months)
EQ-5D	Health related quality of life	Baseline and 6 and 12 post-treatment months	Online
PANAS	Positive and negative affect	Baseline and 6 and 12 post-treatment months	Online
FFMQ	Facets and factors of mindfulness	Baseline and 6 and 12 post-treatment months	Online
PHI	Remembered and experienced well-being	Baseline and 6 and 12 post-treatment months	Online

*Follow-up sessions: Post-treatment, 6 and 12 post-treatment months.

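### The QALY area includes the pre-randomisation EQ-5D and no baseline adjustment is named; adjusting for it would make the QALY difference more precise at no cost

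*Protocol article*

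**What the plan says.** Four statements in the protocol article together define the QALY contrast.

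- **Utility source.** Under Utility scores: "QALYs were calculated on the basis of these scores using the Spanish tariffs of EQ-5D".
- **Measurement times.** Table 1 lists the EQ-5D at "Baseline and 6 and 12 post-treatment months". Unlike the PHQ-9 and SF-12, it is not taken at the post-treatment visit. The Recruitment section places baseline before allocation: "The researcher will collect baseline data and will contact an independent researcher to implement the randomization".
- **Aggregation.** Under Cost-utility analysis, "QALYs were approximated by using the area under-the-curve technique", and under Analysis perspective and time horizon, "The time horizon of the study is 12 months".
- **Contrast.** The ICER is "defined as the ratio between incremental costs and incremental effects measured on QALYs or EQ VAS". The printed equation is cost of strategy 1 minus cost of strategy 2, divided by effectiveness of strategy 1 minus effectiveness of strategy 2.

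The inferential tests named at the end of the same section are chi-square, one-way ANOVA and, in the article's words, "for the test of the T-Student quantitative variables". The only regression mentioned anywhere is the multilevel regression under Analysis of clinical efficacy, which names neither covariates nor QALYs. No adjustment for baseline utility appears in the article.

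**The concern.** An area under the utility curve is not a change score: the starting level is part of the result. With no EQ-5D between baseline and 6 months after treatment, the first interval of a 12-month area cannot be computed without the pre-randomisation value, which treatment cannot affect. Utilities measured later are also likely to correlate with baseline. If the contrast is computed as the section reads, the QALY difference between two arms therefore depends partly on how their baseline utilities happened to fall.

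What is at stake is precision. The QALY difference is the denominator of the ICER, and its uncertainty passes straight into the acceptability curves. The baseline EQ-5D that would remove much of this variation is already collected, but the analysis as described makes no use of it as a covariate.

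**Working it through.** The article states no QALY or ICER figure, so there is none to reproduce.

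**Inputs from the article.** EQ-5D times 0, 6 and 12 months, taken as nominal (Table 1); 60 patients per arm and 25% loss to follow-up, leaving 45 (Sample size); programme length of 4-8 weeks (Interventions).

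**Assumptions, because the article gives neither figure.** Utility SD 0.20-0.25, the same at each visit; a common correlation r between visits of 0.5, with 0.3 and 0.7 as a range.

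**1. Weights.** The trapezoid rule in years gives QALY = 0.25 u0 + 0.50 u6 + 0.25 u12. Follow-up is counted from the end of treatment. If the 4-8 weeks of treatment are added to the first interval, the baseline weight becomes (0.5 + 4/52)/2 = 0.29 to (0.5 + 8/52)/2 = 0.33.

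**2. Size of a chance imbalance.** SE of the baseline difference = SD x sqrt(2/60), which is 0.037 for SD 0.20 and 0.046 for SD 0.25.

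**3. Shift in the QALY difference with no treatment effect.** For a baseline difference d0, the expected shift is d0 x (0.25 + 0.75r). At r = 0.5 the coefficient is 0.625, made up of two parts:

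| Part | Coefficient | Shift for a one-SE imbalance |
|---|---|---|
| Direct baseline weight | 0.25 | 0.009-0.011 |
| Correlation with later visits | 0.375 | 0.014-0.017 |
| Total | 0.625 | 0.023-0.029 |

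With 45 per arm the SE of the baseline difference is 0.042-0.053 and the total shift is 0.026-0.033.

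**4. Precision with and without adjustment.** In units of SD squared, Var(QALY) = 0.375 + 0.625r and Cov(QALY, u0) = 0.25 + 0.75r. The adjusted variance is Var minus Cov squared.

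| r | Var | Cov | Adjusted variance | SE ratio | Reduction in SE |
|---|---|---|---|---|---|
| 0.3 | 0.5625 | 0.475 | 0.337 | 0.77 | 23% |
| 0.5 | 0.6875 | 0.625 | 0.297 | 0.66 | 34% |
| 0.7 | 0.8125 | 0.775 | 0.212 | 0.51 | 49% |

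At r = 0.5 and 60 per arm, the SE of the QALY difference falls from 0.030-0.038 to 0.020-0.025. The variance ratio is 0.6875/0.297 = 2.3, so the unadjusted contrast would need about 2.3 times as many patients for the same precision.

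**5. Simulation check.** With no treatment effect, 45 per arm, SD 0.20-0.30 and r 0.4-0.6, the raw QALY difference depended on the baseline difference with slope 0.55-0.71. After regression adjustment the slope was about 0 (-0.02 to 0.01). At SD 0.25 and r = 0.5, the SD of the estimated difference fell from 0.043 to 0.029.

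**The case against.** The strongest reply is that the printed equation is only the textbook definition of an ICER. It does not say how the difference in effectiveness is estimated, and an adjusted difference fits it unchanged. The paragraph on tests is general and not tied to QALYs, and a fuller analysis plan might name covariates. This stands in part: the article does not forbid adjustment. But it does go into detail on the QALY method, the contrast and the tests, and someone following that text would compute an unadjusted difference.

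A reader might also draw three stronger conclusions that the documents do not support.

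- **That the QALY difference is biased.** It is not. Randomisation makes baseline imbalance zero on average, and chance imbalance is part of the sampling variance that the acceptability curves are meant to show. What remains is dependence on the imbalance in the one trial that is run, and avoidable variance.
- **That a shift of 0.023-0.029 is as large as the gain to be expected, or would reverse the sign of the ICER.** The article gives no expected QALY gain, so there is nothing to compare it with.
- **That adjustment gives two arms with identical change but different baselines the same effect.** If every visit differs by d0, the area differs by d0. At r = 0.5 regression removes 0.625 d0 and leaves 0.375 d0.

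It is also true that most of the shift (0.375 of the 0.625 coefficient) is ordinary correlation between baseline and follow-up, which would affect any unadjusted follow-up outcome. Only the 0.25 part is particular to the area.

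**Conclusion.** The point holds as a free improvement in precision to a secondary analysis. As described, the QALY contrast gives weight to the pre-randomisation utility and names no adjustment for it. The estimate is unbiased over repeated trials but needlessly imprecise, and in a given trial it moves with chance imbalance.

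Adjustment would cut its standard error by about a third, with a range of 23% to 49% across the correlations considered. The percentages depend on the assumed correlation and on equal SDs across visits; the absolute shifts depend also on the assumed SD of 0.20-0.25. The weight of 0.25 rests on nominal times and on reading the area as starting at baseline, which the EQ-5D schedule makes necessary. The primary PHQ-9 analysis is not affected.

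**What to change.** Add one sentence to the Cost-utility analysis section. Incremental QALYs for each pair of strategies are estimated by regressing each patient's QALY on arm and baseline EQ-5D utility; the adjusted difference is the denominator of the ICER; and the acceptability curves come from resampling the same model. If the EQ VAS is used as the effect in the same way, adjust for its own baseline value.

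The baseline EQ-5D is already collected, so this needs no new data, visits or patients.
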